### 3.2. Randomization 

Patients will be randomly allocated in a 1:1:1 ratio to one of three groups: arm A (LNG-IUD), arm B (LNG-IUD plus metformin), or arm C (LNG-IUD plus metformin and liraglutide). This randomization will be conducted by an internet-based, remote third-party statistician who is blinded to the study and participant details. The recruiting physician will be trained and provided with detailed instructions on the recruitment protocol. The objective of randomization is to eliminate selection bias. Trial design is summarized in Figure 1. 

### 3.3. Treatment of Adverse Events

Local investigators will handle any adverse events in accordance with current good clinical practice guidelines. Each adverse event will be documented in a case report form, detailing its nature, onset and resolution times, severity, treatment, and outcome. Follow-up examinations may be conducted as needed to ensure patient safety. If a participant shows signs of harm or ineffectiveness, they will be removed from the study by the overseeing physician. These participants’ results will be analyzed separately as a non-pathological complete remission non-pCR group.

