### 2.5. Sample Size

For both endometrium hyperplasia and endometrial cancer groups, a parallel, 3-group design will be used to assess whether there is any difference in the rates between the groups. The two-sided hypotheses will be evaluated with the chi-square test, with an overall Type I error rate (α) of 0.05. For the sample size calculations, the response rate for arm A (LNG-IUD) is expected to be 58.9%, while the response rates for both arms B and C (LNG-IUD plus metformin and LNG-IUD plus metformin plus liraglutide) are expected to be 86.7% based on the results of [18]. To reach at least 80% power with equal group size, the sample size needed is 33/group. Additionally, 24% of the participants are expected to be drop out [19], resulting in an increased target sample size of 44 participants/group (total sample size = 264).

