### 3.8. Follow-Up Evaluations

During the 3-month follow-up, patients with progressive endometrial pathology will be withdrawn from the trial. Those showing complete response, partial response, or stable disease will continue to be monitored and undergo further evaluation after 3 months. At the 6-month follow-up, patients demonstrating progressive disease or recurrence in endometrial pathology will be withdrawn from the trial, while those with complete response, partial response, or stable disease will undergo another 3-month follow-up. Similarly, at the 9-month follow-up, patients exhibiting progressive disease or recurrence will be withdrawn, while those with complete response, partial response, or stable disease will be followed up again after 3 months. During the 12-month follow-up, patients with partial response, progressive disease, stable disease, or recurrence in endometrial pathology will be withdrawn from the trial and recommended for hysterectomy. Although the study duration is one year, treatment and patient follow-up will be long-term. Hysterectomy will be advised for patients who do not achieve complete pathological response within one year. Patients with fertility requirements or those unwilling to undergo hysterectomy will be closely monitored for signs of recurrence.

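### Section 3.3 says women removed for harm or ineffectiveness are analysed separately; taken literally, this forms a post-randomisation group outside the three arms and can bias the primary comparison in either direction

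*Protocol article*

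**What the plan says.** The primary outcome is complete pathological remission (section 2.3.1), compared across three arms randomised 1:1:1 in an open-label trial (sections 2 and 3.2).

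Section 3.3 provides that a participant showing signs of harm or ineffectiveness is taken out of the study by the overseeing physician. It then gives an analysis rule for these women: their "results will be analyzed separately as a non-pathological complete remission non-pCR group".

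Section 3.8 withdraws women with progression at 3 months, and women with progression or recurrence at 6 and 9 months. At 12 months, "patients with partial response, progressive disease, stable disease, or recurrence in endometrial pathology will be withdrawn from the trial and recommended for hysterectomy". It does not mention analysis sets.

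Section 2.5 sets the planning basis. The significance level is 5% overall, and the test is named: "The two-sided hypotheses will be evaluated with the chi-square test". The control rate, in percent, reads: "the response rate for arm A (LNG-IUD) is expected to be 58.9". Arms B and C are both planned at 86.7%, a figure taken from a cited study. The group size is then derived from a power target: "To reach at least 80% power with equal group size, the sample size needed is 33/group". This is raised to 44 because "24% of the participants are expected to be drop out". The section does not say whether women removed by a physician are among that 24%.

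**The concern.** A woman removed for ineffectiveness is, in most cases, a failure of the primary endpoint. If she is analysed apart from her arm, membership of the analysed arm depends on what happened after randomisation, and on the judgement of a physician who can know the allocation. Section 3.2 gives the elimination of selection bias as the purpose of randomisation; a literal reading of section 3.3 would let it back in.

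The sentence also pulls two ways. Separate analysis suggests a fourth group. The label non-pCR suggests the failure category of the binary outcome, which would leave the woman in her arm's denominator. These give two different primary analyses from the same data. The choice between them should be fixed before outcomes are known, and section 4 has an oversight committee reviewing unblinded outcome data at least twice a year.

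**Working it through.** **1. The plan's own figure.** Inputs from section 2.5: rates 0.589, 0.867, 0.867; three-group chi-square test, 2 df; α = 0.05.
- Mean rate: (0.589 + 0.867 + 0.867)/3 = 0.7743.
- Noncentrality at n per group: n × Σ(pᵢ − 0.7743)² / (0.7743 × 0.2257).
- n = 32: noncentrality 9.44, power 79.1%. n = 33: noncentrality 9.73, power 80.4%. So 33 per group is reproduced.
- Dropout: 33/0.76 = 43.4, rounded up to 44. Total: 44 × 3 arms × 2 diagnoses = 264.

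The sample size is not in dispute. It assumes that 41.1% of arm A and 13.3% of arms B and C are non-responders among those analysed.

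**2. Literal reading, equal removal.** Let f be the share of non-responders set apart in every arm (assumed). The observed rate is p / [p + (1 − p)(1 − f)]. For f = 0.5: 0.589/(0.589 + 0.411 × 0.5) = 0.741 and 0.867/(0.867 + 0.133 × 0.5) = 0.929.

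| f | Arm A | Arms B, C | Difference (points) | Power from 33/group, simulated |
|---|---|---|---|---|
| 0 | 58.9% | 86.7% | 27.8 | about 80% |
| 0.25 | 65.6% | 89.7% | 24.0 | about 70% |
| 0.50 | 74.1% | 92.9% | 18.7 | about 55% |
| 0.75 | 85.1% | 96.3% | 11.2 | about 29% |

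**3. Literal reading, unequal removal, no true effect.** Assume true pCR of 60% in two arms, with 5% of all women in one and 15% in the other removed, all of them non-responders.
- Observed rates: 0.60/0.95 = 63.2% and 0.60/0.85 = 70.6%.
- From 44 per arm, about 42 and 37 remain; the exact rejection probability of the pairwise chi-square test is 10.5%.
- From 88 per arm (both diagnoses combined), 84 and 75 remain; it is 16.6%.
- Equal removal of 10% in each arm (0.60/0.90 = 66.7%; 40 or 79 left per arm) gives 4.8% and 5.2%.

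For the planned three-group test, simulated at 44 per arm with 58.9% in every arm, the false-positive rate by f in arms A/B/C is:
- 0.2/0.2/0.2: 5.0%
- 0.1/0.2/0.3: 7.3%
- 0.1/0.3/0.5: 16.7%
- 0.5/0.1/0.1: 19.9%

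The last case favours arm A and the two before it favour arm C, so the direction is not fixed.

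**4. Power if removed women stay in their arm as non-pCR (44 per arm, 2 df).** If they are already among the assumed non-responders, the rates are unchanged and power is 90.7%. If an extra share d in every arm counts as failure, each rate becomes p(1 − d):

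| d | Arm A | Arms B, C | Power |
|---|---|---|---|
| 5% | 56.0% | 82.4% | 83.6% |
| 10% | 53.0% | 78.0% | 75.5% |
| 24% | 44.8% | 65.9% | 53.7% |

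**The case against.** The strongest reply is that the sentence itself labels these women non-pCR, the failure category of the primary outcome. Read that way, they count as failures, nobody leaves the denominator and the bias in steps 2 and 3 does not arise. Section 2.5 supports this reading, because its rates presuppose non-responders among the women analysed. This stands, and it limits the point to what the sentence permits. It does not explain what analysing them separately means, and no other section settles it.

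A reader might go further and infer that failures do leave the denominator, that every section 3.8 withdrawal is an exclusion from analysis, and that removed women make up the 24%. The documents support none of these:
- Section 3.8 is a follow-up rule. Its withdrawals follow a study histology result, so the failure has already been observed, and the 12-month one falls at the last scheduled assessment.
- Section 2.5 does not link physician removal to dropout.
- Setting all non-responders apart, which would give 100% in every arm, contradicts the planning rates.

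It may also be said that unequal removal is speculative. It is. Metformin is given only in arms B and C and liraglutide only in arm C, so removal for intolerance could be more frequent there; if the added drugs work, removal for ineffectiveness would be more frequent in arm A. The abstract expects good tolerability.

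Finally, analysis sets are commonly left to an analysis plan or full protocol that is not shown, so their absence here is no fault. The point rests only on the rule that section 3.3 does state.

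**Conclusion.** The point holds as a defect of a stated analysis rule, not as a demonstrated bias. Section 3.3 can be read as placing women removed for harm or ineffectiveness outside their randomised arms, which conflicts with its own non-pCR label and with the basis of section 2.5. Because the sentence decides the denominator of the primary outcome, it should be corrected before any outcome data are compared.

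If the literal reading were followed, equal removal would pull the difference towards zero (27.8 points down to 11.2 when three quarters of non-responders are set apart). Unequal removal could create a difference in either direction; in the examples, false-positive rates run from about 7% to 20%. Every removal share is an assumption, because the protocol gives none.

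**What to change.** Replace the analysis sentence in section 3.3 with wording to this effect: for the primary outcome every randomised woman is analysed in her allocated arm; a woman removed for harm, ineffectiveness or progression before reaching pCR counts as non-pCR in that arm; any separate summary of removed women is descriptive only. Add to section 3.8 that withdrawal does not take a woman out of the analysis. No clinical removal or withdrawal rule needs to change.

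The edit is a few sentences and has two costs. The endpoint then treats removal for harm as failure whatever the histology, and the protocol should say so. Power also depends on how far removed women overlap with the assumed non-responders: at 44 per arm it is 90.7% with full overlap, and 83.6%, 75.5% or 53.7% if an extra 5%, 10% or 24% in every arm count as failures. The last figure is a worst case that counts the whole dropout allowance as failures on top of the planning rates, which the proposed wording does not require. Section 2.5 should state which assumption it uses.

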#### 2.3.1. Primary Outcome

The primary outcome is the complete pathological remission of endometrial hyperplasia or early stage endometrial cancer in response to the therapy of LNG-IUD plus metformin and combined with liraglutide. 

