### 3.4. Criteria for Discontinuing or Modifying Allocated Interventions

The criteria for the discontinuation of trial medication are as follows.

A participant chooses to withdraw from the study or revokes their consent. Participants may leave the study at any time for any reason without facing consequences.Cancelation of the entire study.Discontinuation of the protocol treatment if it fails to achieve remission based on the following criteria: no treatment response or complete pathological response (pCR) within one year; disease progression at any time; or relapse after remission.Occurrence of severe adverse events, potentially related to the medication (e.g., hemorrhagic shock due to massive vaginal bleeding, severe allergic reaction, thrombosis, liver function impairment), or the diagnosis of a new malignancy (e.g., breast cancer). These events will be assessed by two chief physicians before discontinuing the trial.Any circumstance where the physician determines that treatment with LNG-IUD, metformin, or liraglutide cannot be continued.

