### 3.7. Efficacy Assessments 

Medical consultations regarding diabetic medication will occur in the second month to evaluate the tolerance of metformin or liraglutide. At 3, 6, 9, and 12 months following treatment initiation, a series of assessments will be conducted, including histology assessments to rule out disease progression and vaginal ultrasound assessments to measure endometrial thickness and invasion. If pathological complete remission(pCR) is attained, patients will receive guidance to remove the LNG-IUD and discontinue liraglutide if pregnancy is desired. Metformin may be continued without restrictions if tolerated.

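### Section 3.3 labels every woman removed for harm or ineffectiveness as non-pCR and analyses her separately, whatever her histology and outside any stated link to her randomised arm

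*Protocol article*

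**What the plan says.** Section 2.3.1 makes the endpoint histological: "The primary outcome is the complete pathological remission of endometrial hyperplasia or early stage endometrial cancer". It names no tolerability component and no time point.

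Section 3.3 sets the handling rule: "If a participant shows signs of harm or ineffectiveness, they will be removed from the study by the overseeing physician". The next sentence says that the results of these women are to be "analyzed separately as a non-pathological complete remission non-pCR group". Harm and ineffectiveness share one label.

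A remission can be on file before removal. Section 3.7 states: "At 3, 6, 9, and 12 months following treatment initiation, a series of assessments will be conducted, including histology assessments". At month 3, Section 3.8 keeps responders in the trial: "Those showing complete response, partial response, or stable disease will continue to be monitored and undergo further evaluation after 3 months". It does the same at months 6 and 9.

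The stopping criteria in Section 3.4 include "Occurrence of severe adverse events, potentially related to the medication" and "Any circumstance where the physician determines that treatment with LNG-IUD, metformin, or liraglutide cannot be continued". The same section counts relapse after remission as a failure of treatment, and Section 3.8 withdraws women with recurrence at months 6, 9 and 12.

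**The concern.** The non-pCR label fits a woman whose disease did not respond. It does not fit a woman in documented remission who is removed for an adverse event, and some listed triggers, such as thrombosis or a new malignancy, say nothing about the endometrium. For her, the label contradicts the pathology on file.

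The word *separately* adds a second problem. It may describe a fourth analysis group outside the randomised arms, or only a descriptive listing of women who are still counted as failures in their arms. These give different primary results, and the sentence fixes neither. The trial is open label, so the decision to remove a woman is taken with her arm known. A rule that turns removal into a change of outcome or of denominator therefore gives that decision direct influence on the primary comparison.

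**Working it through.** **1. The rule applied to three records.**
- pCR at months 3 and 6, severe drug reaction at month 7, removed: Section 3.3 labels her non-pCR.
- No response, removed for ineffectiveness: same label, same group.
- pCR at month 3, no adverse event, still in remission at month 12: pCR.

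The first and second women share a group although their histology is opposite.

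**2. The plan's own sample size (Section 2.5).** Inputs: 58.9% in arm A, 86.7% in B and C, two-sided alpha 0.05, chi-square test on three groups.
- Mean rate p̄ = (0.589 + 0.867 + 0.867)/3 = 0.7743.
- Noncentrality λ = n·Σ(pᵢ − p̄)²/[p̄(1 − p̄)] = 33 × 0.0515/0.1747 = 9.73.
- Power on 2 df is 80.4% at 33 per group and 79.1% at 32, so 33 reproduces.
- 33/0.76 = 43.4, rounded up to 44; 44 × 3 arms × 2 disease groups = 264.

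The margin above 80% is thin, and one woman in 33 is 3.0 percentage points.

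**3. The two readings.** Let p be an arm's pCR rate when pCRs before removal count, h the share removed, and r the share of removed women with a pCR on file.
- Counted as failures: p − hr.
- Excluded from the arm: (p − hr)/(1 − h), which exceeds p exactly when r < p.

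With p = 0.867 (h and r are assumed):

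| h | r | as failures | excluded |
|---|---|---|---|
| 5% | 0.50 | 84.2% | 88.6% |
| 10% | 0 | 86.7% | 96.3% |
| 10% | 0.50 | 81.7% | 90.8% |
| 10% | 0.867 | 78.0% | 86.7% |
| 10% | 0.90 | 77.7% | 86.3% |

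**4. Effect on the C minus A difference (planned 27.8 points).** Assume 10% removed in C, 5% in A, and r = 0.5 in both.
- As failures: A = 58.9 − 2.5 = 56.4%; difference 81.7 − 56.4 = 25.3 points.
- Excluded: A = 56.4/0.95 = 59.4%; difference 90.8 − 59.4 = 31.4 points.

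The same removals move the contrast in opposite directions.

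**5. How far r depends on timing.** Assume first pCR is seen at months 3/6/9/12 in 25/35/25/15% of responders.
- Removals even over 12 months: r in arm C = 0.867 × (0 + 0.25 + 0.60 + 0.85)/4 = 0.368, so 10% removal relabels 3.7 points.
- 70% of removals in the first three months, the rest even: r = 0.10 × (0.217 + 0.520 + 0.737) = 0.147, so 10% removal relabels 1.5 points.

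**6. Power under the failure reading, 33 per group.** With assumed shares of responders relabelled in A/B/C:
- 5/5/5%: power 71.1%, C minus A 26.4 points.
- 0/2/4%: power 69.5%, C minus A 24.3 points.
- 0/5/10%: power 52.3%, C minus A 19.1 points.

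**The case against.** **Counting removal for an adverse event as non-response is a recognised composite strategy.** This stands, if the strategy is declared. Here it is not declared: Section 2.3.1 defines pathology alone, and Section 3.3 adds a separate analysis, which a composite would not need.

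**An early pCR is provisional.** This also stands. Section 2.3.2 lists the histological changes at months 3, 6 and 9 as secondary outcomes, which points towards month 12 for the primary, and Sections 3.4 and 3.8 treat relapse as failure. A woman removed at month 7 has no month-12 status. A reader might infer that any pCR before removal must count as success; the documents do not establish that. They equally give no basis for overriding the histology without saying so.

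**A reader might infer that the rule penalises the arms with added drugs,** since one agent in arm A, two in B and three in C could prompt stopping. The documents do not support this as a conclusion. No removal rate is given by arm, metformin may be given at the maximum tolerated dose, the listed severe events are not all specific to the added drugs, and the abstract anticipates minimal adverse effects. Early dose titration and a tolerance review in month 2 suggest that many removals could precede the first histology. Above all, the direction depends on the meaning of *separately*: if removed women leave the arms, the added-drug arms can gain.

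**The analysis plan may settle it.** It could fill a gap, but this is a stated rule, which would still need correcting.

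**Conclusion.** The point holds as a badly fixed rule. Section 3.3 pools harm with ineffectiveness, assigns one label regardless of histology, and leaves open whether the women remain in their randomised arms. Under either reading a documented remission is lost as a success in its arm, which Section 2.3.1 gives no ground for.

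Neither direction nor size of bias can be established. The figures above rest on assumed removal shares, prior-pCR shares and timing, and show only that a few women can matter at 33 per group. If removals for harm are as rare as the protocol hopes, that part of the effect will be small. The correction is worth making because it is cheap and removes an ambiguity that would otherwise be resolved after open-label data are seen.

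**What to change.** Replace the last sentence of Section 3.3 so that:

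- all women removed for harm or ineffectiveness are analysed in their randomised arm;
- their primary-outcome status follows one pre-specified rule based on recorded histology, consistent with Sections 2.3.1, 3.4 and 3.8, stating how relapse after remission counts, and applied identically in all arms;
- removal for harm is kept apart from ineffectiveness and reported by arm as a safety outcome;
- both codings of women with a pCR before removal are presented: counted as pCR, and counted as non-pCR as a declared composite. One is named in advance as primary, the other as sensitivity analysis.

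The cost is one sentence, the matching derivation and a little more analysis work. No new data or procedures are needed, and clinical management is untouched. One downside should be stated: carrying a pre-removal pCR forward may be lenient, because a later relapse would not be seen, whereas women who stay can still lose their remission. Showing both codings makes that visible.

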### 3.4. Criteria for Discontinuing or Modifying Allocated Interventions

The criteria for the discontinuation of trial medication are as follows.

A participant chooses to withdraw from the study or revokes their consent. Participants may leave the study at any time for any reason without facing consequences.Cancelation of the entire study.Discontinuation of the protocol treatment if it fails to achieve remission based on the following criteria: no treatment response or complete pathological response (pCR) within one year; disease progression at any time; or relapse after remission.Occurrence of severe adverse events, potentially related to the medication (e.g., hemorrhagic shock due to massive vaginal bleeding, severe allergic reaction, thrombosis, liver function impairment), or the diagnosis of a new malignancy (e.g., breast cancer). These events will be assessed by two chief physicians before discontinuing the trial.Any circumstance where the physician determines that treatment with LNG-IUD, metformin, or liraglutide cannot be continued.

### 3.5. Discontinuation of the Study

The study will be terminated early if the Institutional Review Board (IRB) identifies any of the following: serious adverse drug effects (e.g., unresponsive abnormal liver function, thrombosis, hemorrhagic shock due to massive bleeding, severe allergic reaction); diagnosis of a new malignancy; participants encountering unexpected, significant, or unacceptable risks (such as death); or the determination of treatment ineffectiveness.

### 3.6. Baseline Assessments 

Baseline assessments will adhere to the trial’s standard operating procedure (SOP). During the visit, a urine pregnancy test will be conducted. If the result is negative, LNG-IUD insertion will be performed following protocol guidelines. Blood tests and oral glucose tolerance tests will be administered at 0–60–120 min intervals to assess glucose and insulin levels. Education provided by a dietitian and physiotherapist will emphasize the importance of adopting healthy dietary habits and regular physical exercise. Participants will be encouraged to maintain an exercise diary. Medical consultation and the initiation of diabetic medications will also commence during this phase.

